**Application**  
**to the assessment of ethical and legal questions**  
**of a medical research project on humans**

**I. General information**

**1. Title of the research project**

Pilot study (expanded access) to evaluate the compatibility of a ring covered with an amniotic membrane (AmnioClip) for placing on the ocular surface

## 5. Financing

☒ with sponsor                      ☐ without sponsor

Name of the sponsors

The manufacturer of the holder and clamping device is FORTECH UG (with limited liability),  
[name], Germany

## 6. Was an application with the same content already been filed in another ethics committee? And if so, which? (The vote of the other ethics committee is attached.)

Yes, ethics committee of the university hospital Halle, Germany

## II. Research project

### 1. Brief summary of the project

Surface defects of the eye are difficult to treat and occur after injuries such as acid burns, or are caused by autoimmune diseases such as rheumatoid arthritis, in which the cornea with ulceration is involved particularly at higher age. Even after penetrating keratoplasty, disturbances of the epithelization can occasionally occur. The use of commercially available eye drops to foster wound healing is generally not very effective, because they cannot support proliferation of the corneal epithelium. The treatment is usually tedious. Clinical trials with growth factor containing eye drops were carried out many years ago, but did not provide any results. Todate, locally applicable drugs based on the basis of a growth factor are not available. Thus, disturbances in wound healing require consuming and tedious ointment and drop therapies. This also involves long stays at hospi-tals for these patients. During the treatment, cloudiness often occurs in the area of the corneal stroma. Thus a visual worsening or even blindness in the affected eye may be a consequence.

In the clinical practice, surgical application of an amniotic membrane by suturing onto the ocular surface has been proven as a very good alternative. The amniotic membrane is obtained after cesarean birth (cesarean section) and can be stored for a certain time in special media or freeze-dried. Meanwhile, there are many trials on the effectiveness of this method (see accompanying review article). The amniotic membrane is sutured onto the ocular surface of the patient, i.e. the membrane is fixed with a continuous thread or with individual sutures. Amniotic membrane is considered to be poorly immunogenic and it is obviously rich in growth factors, so that the healing process strongly is promoted under normal circumstances. The clinical results are significantly better in comparison to a

conventional ointment or drop therapy or in comparison to the application of contact lenses.

The disadvantage of the surgical method is that amniotic membranes often need to be re-attached with sutures (more than once) because they can detach from the ocular surface. In addition, the threads often cause pain to the patients, so that contact lenses have to be put on in addition. The re-suturing of a membrane also means another surgical intervention on the conjunctiva, which should be impaired as little as possible. In addition, a regional block anesthesia or general anesthesia has to be performed.

The pilot study to test an amniotic holder (AmnioClip) means an optimization of the therapy, since a ring system in which the amniotic membrane is clamped and which can be placed onto the ocular surface without sutures has several advantages. First, it facilitates the handling of the membrane for the surgeon. Second, the ring does not need to be sutured, but is worn similar to a large contact lens, and thus saves the affected persons the expensive suturing and the accompanying damage to the conjunctiva. The positioning of the membrane requires only a drop anesthesia, and the AmnioClip is not supposed to cause postoperative pain, because it is known that large contact lenses or so-called Illig-shells are well tolerated by the eye.

The pilot study is based on these abovementioned points, namely the easier handling of the amniotic membrane, the greater comfort for the patients and the possibility of an easy and rapid exchange of the membrane, if required e.g. in the course of a chronic disease.

In comparison to the standard therapy, suturing of the membrane to the diseased ocular surface, the new procedure of treatment has the advantage that the membrane is placed on the ocular surface by means of the holder, and no invasive surgical suturing techniques are necessary. This significantly simplified treatment can take place outside an operating room. An exchange of the membrane is rapidly done and can occur more frequently if required. This potentially improves the success.

The proposed project is acceptable from an ethical point of view, since it is already known that large contact lenses or scleral shells are compatible on the eye surface. The insetion of the amniotic membrane holder AmnioClip into the palpebral fissure can be controlled by means of a slit-lamp examination. The removal of the amniotic holder AmnioClip is possible at any time without problems. This is where the clinical relevance of the pilot study comes to the fore. A ring covered with an amnion which is placed as a contact lens on the eye may be inserted or removed at any time without any surgical effort.

Together with the spanned amniotic membrane, the amniotic membrane holder can be distributed by eye banks or companies to hospitals or surgeries.

The observation of a placebo group is not necessary, because suturing of an amniotic membrane has been enforced through many trials and observations against an ointment therapy.

Aim of the project:

The primary objective of this project is to examine the mounting and compatibility of the amniotic membrane holder including the amniotic membrane (AmnioClip) in the eye of the patient.

The secondary objective of the study is to examine to what extent the underlying disease can be improved during the observation period (1 week). This is done without a control group.

**2. Type of the research project\***

|                   |                                     |                       |                          |
|-------------------|-------------------------------------|-----------------------|--------------------------|
| therapeutic trial |  | therapy               |  |
| prophylaxis       |             | human experimentation |  |
| diagnostics       |             | miscellaneous         |  |

**3. Is it a drug testing?\***

yes ☐ no ☒;

if so, for which phase of the drug testing is the drug to be tested approved,

- a) for the indication to be tested ☐ yes ☐ no  
 b) for another indication ☐ yes ☐ no if so, for which?

**4. Is it a research project, to which**

- a) the Medicines Act ☐  
 b) the Radiation Protection Regulation ☐  
 c) the X-Ray Regulation ☐  
 d) the Medical Devices Regulation ☐  
 e) the Medical Product Law ☒

can be applied?\*

On item a) Thereby, attention is to be paid to § 67 of the Medicines Act.

(Notification obligation to the regional council)

In the case of radiological and / or nuclear medicine investigations only caused by the research project, we ask you to ensure that an authorization in accordance with the Radiation Protection Act by the relevant regional council has to be available.

**5. Type of the research project\* :**

|             |                                     |                          |                          |
|-------------|-------------------------------------|--------------------------|--------------------------|
| open        |  | randomized               |  |
| blind       |             | multicenter              |  |
| doubleblind |             | case study               |  |
| comparative |             | pilot study              |  |
|             |                                     | national / multinational |  |

**6. Procedure of the clinical trial see III****III. Questions to patients and probands**

10 persons are involved in the pilot study.

It is planned to involve the patients starting Feb 2011.

The postoperative observation period amounts one week. Dependent upon compatibility, the postoperative observation period may be extended to 4 weeks.

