### ***Following visits (day 8 to 30)***

Depending on the individual assessment, the amniotic membrane holder may be left on the cornea for more than 1 week. In this case, a final visit will be performed at a later time, but at least after 4 weeks. At this visit, the holder is removed permanently, and there is a clinical slit lamp examination.

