## **Secondary target figure**

The secondary target figure is aimed towards the support of wound healing by the applied amniotic membrane clamped into AmnioClip. Provided that the amniotic membrane holder is well tolerated, it will be assessed whether an improvement has occurred or not at the end of the observation period.

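### The protocol contradicts itself on when improvement is read: day 7 by its aims, or the end of a period that may be extended to about 4 weeks in selected patients

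*Protocol*

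**What the plan says.** Several places in the protocol bear on the read time.

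- **II.1, aim of the project.** The secondary objective is to examine "to what extent the underlying disease can be improved during the observation period (1 week"), without a control group.
- **III, Questions to patients and probands.** "The postoperative observation period amounts one week". The next sentence reads: "Dependent upon compatibility, the postoperative observation period may be extended to 4 weeks".
- **Visit 5 (day 7).** The holder is removed, a final eye examination is done and subjective perception is recorded. The trial is described as, strictly speaking, finished then.
- **Following visits (day 8 to 30).** This section opens a second route to a longer period: "Depending on the individual assessment, the amniotic membrane holder may be left on the cornea for more than 1 week". For these patients the final visit moves to a later date, no earlier than 4 weeks. Removal and a slit-lamp examination are the only items listed for it.
- **Assessment of the effectiveness.** Patients are seen daily, and success on the primary target requires four points to hold over one week.
- **Secondary target figure.** If the holder is well tolerated, "it will be assessed whether an improvement has occurred or not at the end of the observation period". No day is named.

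**The concern.** The same term, observation period, has one fixed length in the aims and a variable length in section III, and the secondary endpoint is tied to its end. Read literally, the time at which a patient's healing is judged depends on compatibility, which is the primary outcome, or on an individual assessment for which no criterion is given. Both are known to the investigator in this open study before the read time is settled.

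An epithelial defect has more opportunity to close in 4 weeks than in 1. A proportion improved that mixes the two times answers neither the 1-week nor the 4-week question. With no control group, nothing in the design separates the effect of a longer window from the effect of the membrane.

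A second gap follows from the visit schedule. Visit 5 pairs the final examination with removal of the holder. Where removal is postponed, the text does not say whether the day-7 examination and the record of subjective perception still take place. A later analysis plan cannot recover an examination that was not made.

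**Working it through.** **Step 1: the possible read times.** The only sample-size statement is "10 persons are involved in the pilot study". There is no derived figure to reproduce, so the first check is textual.

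| Source | Implied read time for improvement |
|---|---|
| II.1, aims | 1 week |
| III, first sentence on follow-up | 1 week |
| Visit 5 | day 7, trial then complete |
| III, next sentence | up to 4 weeks, depending on compatibility |
| Following visits | 4 weeks or later, depending on individual assessment |
| Secondary target figure | whenever the period ends |

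The first three rows agree with one another. The next two do not agree with them, and they differ on whether 4 weeks is a maximum or a minimum. The last row settles nothing.

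**Step 2: how far mixed read times could move the result.** All inputs here are assumptions; none is in the protocol.

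- p7: proportion improved by day 7.
- f: share of assessed patients who are extended to day 28, at first taken as unrelated to healing.
- Healing at a constant rate, with improvement not lost once reached.

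Day 28 is four 7-day intervals, so p28 = 1 − (1 − p7)^4. The reported proportion is r = (1 − f) × p7 + f × p28.

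For p7 = 0.40: p28 = 1 − 0.6^4 = 1 − 0.1296 = 0.870.
- f = 0.3: 0.7 × 0.40 + 0.3 × 0.870 = 0.541.
- f = 0.5: 0.5 × 0.40 + 0.5 × 0.870 = 0.635.

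| p7 (all read at day 7) | p28 | r, f = 0.3 | r, f = 0.5 | r, f = 0.8 |
|---|---|---|---|---|
| 0.20 | 0.590 | 0.317 | 0.395 | 0.512 |
| 0.30 | 0.760 | 0.438 | 0.530 | 0.668 |
| 0.40 | 0.870 | 0.541 | 0.635 | 0.776 |
| 0.50 | 0.938 | 0.631 | 0.719 | 0.850 |
| 0.70 | 0.992 | 0.788 | 0.846 | 0.934 |

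If all 10 patients tolerate the holder, p7 = 0.30 gives an expected 3.0 improved when everyone is read at day 7, and 10 × 0.530 = 5.3 when half are extended.

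**Step 3: who is extended.** A patient not improved at day 7 has a chance of 1 − 0.6^3 = 0.784 of improving in the next three weeks when p7 = 0.40. If u is the share of all assessed patients who are both extended and unimproved at day 7, then r = 0.40 + u × 0.784. With half extended:
- extension unrelated to healing, u = 0.5 × 0.6 = 0.3: r = 0.635, as in step 2;
- only unimproved patients extended, u = 0.5: r = 0.792;
- all improved patients among those extended, u = 0.5 − 0.4 = 0.1: r = 0.478.

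The reported figure could thus lie between about 48% and 79% for one and the same healing process.

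**Step 4: after the fix.** If everyone is read at day 7, r = p7 whatever share is extended.

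**The case against.** The case on the other side is substantial. The aims say 1 week, the basic period is 1 week, and Visit 5 is labelled final and closes the trial. The natural reading is that improvement is judged at day 7 and that days 8 to 30 are optional follow-up. This stands to the extent that the defect is a contradiction and not a settled variable window. It does not remove the defect, because section III extends the very period whose end defines the read time.

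Three stronger readings are tempting, and the protocol does not support them.

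- *Everyone who tolerates the holder is read at 4 weeks, and the others at 1 week.* Extension is optional, and improvement is assessed only where the holder is well tolerated. Any mixing is among tolerating patients, some extended and some not.
- *Extended patients have no day-7 reading, so the primary criterion cannot be judged in them.* Nothing exempts them from Visit 5. The daily visits and the one-week success rule imply a check at day 7, and a decision to leave the holder in presupposes some assessment at about that time. The schedule, however, lists only days 1, 3 and 7 and does not expressly keep the Visit 5 items when removal is postponed. A missing reading is a risk, not a stated fact.
- *The window is chosen according to healing.* The stated trigger is compatibility. Dependence on healing is possible through the individual assessment, but it is an inference.

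The arithmetic rests wholly on assumed values, and the protocol does not state that a pooled proportion will be calculated. If improvement can be lost again, a later reading need not be higher. The outcome is secondary and descriptive, in 10 uncontrolled patients, and no test depends on it. How later readings are reported may properly be left to an analysis plan. The read time and the visits that must take place are set in the protocol itself, and there they conflict.

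**Conclusion.** The point stands as a moderate one. The protocol gives two incompatible read times for its only healing endpoint and lets the later one be chosen after the patient's course is known. If the text is followed literally and healing is cumulative at a constant rate, a true day-7 rate of 40% would be reported as about 54% with 30% of assessed patients extended and about 64% with half extended. From 20%, half extended gives about 40%. These figures show how sensitive the result is to the read time; they do not predict this trial's result. The definition of the primary criterion, fixed at one week, is not in question. What is unclear is whether its day-7 check is secured in extended patients.

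**What to change.** 1. In *Secondary target figure*, name day 7 (Visit 5) as the read time for improvement, in place of the end of the observation period.
2. In *Visit 5* and *Following visits*, state that the Visit 5 assessments (the four success points, the eye examination and subjective perception) are recorded at day 7 in every patient, whether or not the holder stays.
3. Report readings after day 7 separately, as descriptive results with the wear time.
4. Reconcile section III with *Following visits* on whether 4 weeks is an upper or a lower limit, and reconcile the daily visits under *Assessment of the effectiveness* with the listed visits. How long the holder is worn is a clinical matter and is left open here.

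The cost is protocol wording, since the day-7 visit already exists. There is one small drawback: in extended patients the day-7 reading is made with the membrane in place, in the others at removal. The record should state which condition applied, so that the difference is visible when the results are read.

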**Inclusion criteria**

- male and female patients between 18 and 85 years
- epithelial defects of the cornea of different genesis (eg after injury, after acid burns, in autoimmune diseases such as rheumatoid arthritis)
- incipient corneal ulcer, unless there is no bacterial infection
- existence of the declaration of patient consent

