## Exclusion criteria

- visible small palpebral fissure
- inflammatory bacterial diseases a causal factor for epithelial defects
- participation of the patient in another clinical trial within the last 4 weeks prior to the inclusion
- addiction or other diseases which do not allow the person concerned to evaluate the nature, scope and possible consequences of the therapeutic trial
- women who are either pregnant or breast feeding
- women of child-bearing age, except women who meet the following criteria:
  - post-menopausal (12 months natural amenorrhoe or 6 months amenorrhoe with serum FSH > 40 mIU/ml)
  - post-operative (6 weeks after bilateral ovariectomy with or without hysterectomy)
  - regular and correct application of a contraceptive method with an error rate < 7 % per year (eg implants, depot syringes, oral contraceptiva, intrauterine device – IUD). It should be considered that the combined oral contraception – as opposed to purely progesterone preparations – has a failure rate of < 1 %. Hormone coils with a Pearl index < 1 % are safer than copper coils.
  - sexual abstinence
  - vasectomy of the partner
- evidence that the patient presumably does not comply with the trial plan (e.g. lack of cooperation)

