## Procedure of the clinical trial

### *Visit 1 (Screening Visit, Baseline)*

Each participating person has to be fully informed about the therapeutic trial before agreeing to participate in the therapeutic trial. The medical information and education is given personally by the investigating physician as well as in writing by the patient information sheet. Only subsequently to the clarification of all questions, the patient is asked to sign and to personally date two copies of the consent form. Afterwards, one copy of the patient information sheet / consent form is issued to the patient; the second copy shall be preserved in a document file at the trial centre.

The demographic data, anamnesis, and secondary diagnoses are acquired at the visit 1. In addition, an ophthalmological examination is carried out, and vital parameters as well as the body weight are

recorded. Among women of childbearing age, a pregnancy test will be performed. The patient will be enrolled in the therapeutic trial according to the results of verification of the inclusion exclusion criteria.

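### The corneal-ulcer inclusion criterion carries a double negative that literally requires bacterial infection and conflicts with the exclusion list

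*Protocol*

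**What the plan says.** Section III of the Protocol describes the study population in two bullets of the inclusion list. The first covers "epithelial defects of the cornea of different genesis", gives examples of origin, and sets no condition on infection. The second covers "incipient corneal ulcer, unless there is no bacterial infection".

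The exclusion list that follows rules out "inflammatory bacterial diseases a causal factor for epithelial defects". A linking word is missing there. I read it as excluding bacterial disease that caused the defect.

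The Visit 1 section makes both lists operative: "The patient will be enrolled in the therapeutic trial according to the results of verification of the inclusion exclusion criteria". The planned size is given under Procedure of the clinical trial: "10 persons are involved in the pilot study". No other part of the Protocol explains or corrects the ulcer wording.

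**The concern.** The inclusion and exclusion lists should agree on whether a bacterial infection keeps a patient out. Here the inclusion bullet, as worded, demands infection, while the exclusion bullet removes patients because of it. The two bullets also test different things: one asks whether infection is present, the other whether it is the cause. Reading them together therefore does not settle every case.

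At stake is who wears the holder for a week or longer, and whether two people screening the same ulcer patient would reach the same answer. A screening form copied from the list would carry the inversion with it. The population that the results describe would also be unclear for ulcer patients.

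**Working it through.** No figure is at issue, so the check is a truth table built from the two lists.

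**Inputs**
- Ulcer bullet (Protocol, Inclusion criteria): an ulcer qualifies unless infection is absent. In the form *A unless not-B*, A fails when B is false and qualifies when B is true. Here B is that bacterial infection is present.
- Exclusion bullet (Protocol, Exclusion criteria): the patient is out if bacterial disease caused the epithelial defect.
- Enrolment (Protocol, Visit 1): both lists are checked.

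**Literal reading, for a patient with an incipient ulcer**

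| Case | Ulcer bullet | Exclusion bullet | Entry through the ulcer bullet |
|---|---|---|---|
| 1. No bacterial infection | not met | does not apply | no |
| 2. Infection present and causal | met | applies | no |
| 3. Infection present, not causal | met | does not apply | yes |

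Only case 3 passes.

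**Does the exclusion list settle what was meant?** Compare the literal text with two other readings that a screener might adopt. One is that any infection disqualifies an ulcer. The other is that only a causal infection does.

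| Case | Literal text | Any infection disqualifies | Only causal infection disqualifies |
|---|---|---|---|
| 1 | out | in | in |
| 2 | out | out | out |
| 3 | in | out | in |

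Case 2 is out under all three, because the exclusion bullet decides it. Cases 1 and 3 depend on the reading. A screener who assumes a slip and reverses the sentence resolves case 1, but must still guess case 3.

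**The second route.** The epithelial-defect bullet sets no condition on infection. If the two disease bullets are alternatives, case 1 and case 3 patients who have an epithelial defect can enter through it, and the exclusion bullet does not stop them. If the bullets are not alternatives, this route is closed. The layout does not decide the matter: the same list contains age and consent, which every participant must meet, and nothing marks the two disease bullets as either/or.

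**The case against.** The strongest reply is that this is a language slip with little practical effect. The exclusion list shows that bacterial causes were meant to be kept out. The application was made under German law, and the English text has other slips, including the missing word in the exclusion bullet itself. Enrolment follows an ophthalmological examination by a physician, who would probably notice the conflict. Much of this stands: a slip is the likeliest explanation, and the broad intent can be recovered. But any German wording is not at hand, so it cannot be known which text the investigators used, and the recoverable intent does not reach case 3.

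Three stronger readings are tempting, and the documents do not support them.

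- **That the trial openly admits infected ulcers.** This holds for the inclusion bullet in isolation only. Both lists must be checked, and the exclusion bullet bars ulcers whose defect is caused by bacterial disease.
- **That uninfected ulcers cannot enter at all.** They fail the ulcer bullet, but may enter as epithelial defects if the bullets are alternatives. Section II.1 itself mentions corneal ulceration in autoimmune disease, and autoimmune disease is one of the origins listed in the epithelial-defect bullet. The Protocol leaves the route open.
- **That the error has a measurable effect on the success rate or the early-stopping rule.** With 10 participants one patient is 1/10 = 10 percentage points, but that is true of any patient. The documents do not say how many ulcer patients are expected, how often infection is present without being the cause, or how such patients would tolerate the holder. An effect on pain, healing or stopping is conceivable and cannot be sized.

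**Conclusion.** The point holds as an error in the eligibility wording. Taken literally, the ulcer bullet makes bacterial infection a condition of entry and conflicts with the exclusion list. Under both lists only ulcers with a non-causal infection enter through that bullet. Ulcers caused by infection stay excluded, and the status of uninfected ulcers depends on whether the disease bullets are alternatives, which is not stated.

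The size of the problem is qualitative: of three kinds of ulcer patient, the text settles one and leaves two to the reader. No sample size, error rate or analysis is affected. Because enrolment turns on these lists, it still needs correcting.

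The conclusion assumes that the English text is the operative one and that the exclusion bullet, despite its missing word, refers to infection as the cause of the defect. Confidence is high for the contradiction in wording and low for any particular consequence in practice.

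**What to change.** The sponsor and investigator should reconcile the ulcer inclusion bullet with the bacterial-disease exclusion bullet. Which infection rule applies is for them to decide. The text needs three things:

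- one positively worded statement on bacterial infection, used identically in both lists, that says whether presence or causation is meant and so covers case 3;
- a sentence stating whether the epithelial-defect and ulcer bullets are alternatives;
- the same wording on the screening form.

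This should be done before the first enrolment. If patients have already been screened, the trial record should state which reading was applied to ulcer patients. The cost is one or two sentences in the Protocol and the matching line on the form. No recalculation is needed.
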